# For the balance test we include:

- VEA school in village cluster
- Type of roof (improved roof= 1 if roof is finished roofing (i.e. *Metal, Wood, Calamine/Cement fiber Ceramic tiles, Cement, or Roofing shingles*)
- Wall (improved walls = 1 if walls are “finished walls”)
- Floor (improved floor= 1 if floor is “finished floor”)
- ~~Sex of respondent~~
- Household size
- Religion (Catholic = 1)
- Mother tongue
- Marital status 🡺 binary variable for married

# **Subgroup And Spillover analysis**

1. As with many interventions of this kind, it is likely that the VEA program may work differently for different socioeconomic groups. For instance, the program may have relatively larger effects on poorer/vulnerable communities, as compared to communities that are relatively affluent, and it may have larger effects on women than on men. Thus, in addition to estimating the main treatment effects, we will investigate potential heterogeneity of the VEA program based on several pre-treatment (or time-invariant) characteristics related to the VEA program or the local context. Our primary interest for sub-group analysis is to explore gender differences in time collecting water. We have additional exploratory interest in:
2. Province (each of the four provinces).
3. Distance to territory capital (a binary indicator for above or below the median distance for the province).
4. Education (a binary indicator for above or below median formal education of the household head).
5. Conflict history (a binary indicator for above or below the median number of conflict events experienced in a village prior to program onset).

Each subgroup analysis will cover the set of primary outcomes described in Section 4.

We model heterogeneous treatment effects by the following equation:

$y_{ihvc}= \alpha_{s}+\beta_{1}T_{c}+\beta_{2}T_{c}* Z_{c} + {\beta_{3}Z}_{c}+ \varepsilon_{i}$ (2)

where $y_{ihvc}$ is the outcome of interest for respondent *i* in household *h* in village *v* in cluster *c.* at the follow-up survey, defined above. $T_{i}$ is the treatment indicator that takes value 1 for clusters that were randomly assigned to participate in VEA (“treatment clusters”) and 0 for otherwise (“control clusters”). $Z_{c}$ is a vector of baseline characteristics (e.g. gender) by which we are interested in heterogeneous treatment effects. $\beta_{2}T_{c}* Z_{c}$ represents an interaction between the treatment and those characteristics. $\alpha_{s}$ captures stratum-specific fixed effects, where strata are based on province and number of villages in the cluster. $\varepsilon_{i}$ is an idiosyncratic error term. Our main parameter of interest is $\beta_{2}$.

In South Kivu, some treated clusters may be just over 1 km from control clusters. To probe for potential spillovers, we follow Null *et al*. (2018) and test whether primary outcomes were the same in control households with more versus fewer households receiving interventions within a 2 km radius.^[[4]](#footnote-4)^ This will allow us to assess whether spillovers may be a concern for the primary analysis where we focus on direct effects.

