**Table 1. Key outcomes of interest**

| **Outcome Type*** | **Outcome Name** | **Definition** | **Survey** | **Analysis level** |
| --- | --- | --- | --- | --- |
| Primary | Water access | Total time spent collecting water yesterday | Household | Household |
| Primary | Water quality | Primary source of drinking water is improved source (JMP definition) | Household | Household |
| Primary | Water quantity | Total amount of water collected yesterday | Household | Household |
| **Primary** | Sanitation access | Household uses an improved latrine (JMP definition) | Household | Household |
| **Secondary** | Health behavior / Knowledge | Handwashing practices (primarily of caregiver) based on handwashing with soap + water or ash at critical junctures  Knowledge: Caregiver knows how and when to wash hands; what causes diarrhea  Sanitation practices: Cleanliness of household area and latrine (presence of flies and fecal matter); open defecation; observed indicators of toilet use –worn pathway, presence of water; improvements to latrine; disposes of child feces safely (JMP definition)  Water storage practices: has a clean pot for water that is covered | Household | Household |
| **Secondary** | Child health | Percentage of children under 5 years old with diarrhea/fever/coughing in the past two weeks; water-related mortality of children | Household | Child |
| **Secondary** | School attendance | Number of days present per child in past week, conditional on child being enrolled in school | Household | Child |
| **Secondary** | Functional water points | Number of functional improved water points in cluster; number and length of breakdowns; time to fill 5-liter jerry can; year-round availability | Village | Community |
| **Secondary** | Financial cost of water | Household water use expenses in last week | Household | Household |
| **Secondary** | Satisfaction | Satisfaction with access to water | Household | Household |
| **Secondary** | Water governance | Is there a committee that is responsible for water; size of committee and inclusion of minorities; has a water maintenance system; time since visited by health zone; satisfaction with health zone, health area and central govt. | Village | Village |

*Other outcomes not in this list may be analyzed on an exploratory basis.

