**Primary outcomes**

- *Water access:* Amount of time spent collecting water in minutes by the household in the previous day, calculated by summing up all trips x trip times in roster (Q. HH–A.4). Question asks: “How long did it take to fetch the water and come back on this trip, after leaving the house (including traveling there, waiting, and returning)?” for each trip.
- *Water quality*: What is the main source of drinking water for members of your household? (Q. HH–A.1). Binary outcome = 1 if response = 1 (piped into dwelling); 2 (piped into plot); 3 = piped/public tap); 5 (tube well or borehole); 7 (protected spring). Outcome is assigned 0 for all other response. (basic improved water source definition as per JMP)
- *Water quantity:* Total amount of water collected the day before interview in liters (Q. HH–A.4). Number of jerry cans multiplied by the liters in each jerry can, summed over all trips taken in previous day
- *Sanitation access:* Where do members of your household usually go to defecate (Q. HH-F.1). Binary outcome = 1 if response = 1 (flush/pour to piped sewer); 2 (flush/pour to septic tank; 3 (flush/pour to pit latrine), 6 (ventilated improved pit latrine); 7 (pit latrine with slab); 8 (composting latrine). Outcome is assigned 0 for all other responses. This follows the basic improved sanitation definition as per JMP.

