**Secondary and exploratory outcomes**

**Water quality and access**

- Total number of water points in the villages (VL–B.1)
- Total number of functional water points in the villages (VL–B.4)
- Total number of functional improved water points in the villages (VL–B.4.2)
- Total number of breakdowns in functional water points in past 6 months (VL–B.4.11)
- Total length of breakdowns in functional water points in past 6 months (VL–B.4.12)
- Total length of last breakdown in functional water points before reparation (VL–B.13)
- Number of trips to collect water conducted the day before interview by women and children (Q. HH–A.4)
- Distance of primary water source from center of the village (Q. VL–B.4.7)
- Time to fill a 5-liter jerry can at primary water source, in minutes (Q. HH–A.7)
- Average water availability year-round (Q. VL–B.4.22)
- Community perception of water quality (Q. VL–4.26)

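### The leading subgroup question, gender differences in water-collection time, is tied to an outcome defined only as a household total, so the interaction in equation (2) cannot estimate it until minutes are split by the collector's gender

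*Protocol*

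**What the plan says.** Four parts of the protocol bear on this.

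- **Subgroup And Spillover analysis, the question.** "Our primary interest for sub-group analysis is to explore gender differences in time collecting water". Province, distance to the territory capital, education and conflict history follow as additional exploratory interests.
- **Same section, the outcomes and the model.** "Each subgroup analysis will cover the set of primary outcomes described in Section 4". Equation (2) interacts treatment with Z, which "is a vector of baseline characteristics (e.g. gender) by which we are interested in heterogeneous treatment effects". The parameter of interest is the interaction coefficient, beta2.
- **Table 1 and Primary outcomes, the time outcome.** Table 1 gives "Total time spent collecting water yesterday | Household | Household", where the last two entries are the survey and the analysis level. The operational definition is "Amount of time spent collecting water in minutes by the household in the previous day, calculated by summing up all trips x trip times", taken from roster HH-A.4. The Operationalization section states that the primary outcomes are completely pre-specified, so this definition is the one in force.
- **Secondary and exploratory outcomes, Water quality and access.** The one collection outcome that refers to who went is "Number of trips to collect water conducted the day before interview by women and children", from the same roster.

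**The concern.** The question concerns the people who fetch water, but the outcome assigned to it adds those people together. The stated question, outcome, model and parameter therefore do not fit one another. This goes beyond detail left for later, because the document is itself the pre-analysis plan and fixes all four.

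The aim in Hypotheses/Evaluation Questions is a lower burden of collecting water, with women and girls singled out. The subgroup analysis is where that part of the aim would be examined. If the outcome is not defined by gender in advance, an analyst must choose a construction after seeing the data, and several are possible.

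**Working it through.** The plan gives no figure to reproduce. The check is whether beta2 can equal the quantity of interest.

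**Definitions.** For household h, let F be the minutes collected by female members and M the minutes collected by male members. The protocol's outcome is y = F + M. Let the treatment effects on F and M be dF and dM.

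- Equation (1) on y estimates dF + dM.
- The gender question asks for dF - dM.

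The sum does not determine the difference. With assumed minutes, a total effect of -25 arises from each of these:

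| dF | dM | dF + dM | dF - dM |
|---|---|---|---|
| -20 | -5 | -25 | -15 |
| -12.5 | -12.5 | -25 | 0 |
| -5 | -20 | -25 | +15 |

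Effects can also run in opposite directions. If female time falls from 60 to 40 and male time rises from 10 to 20 (assumed), the total goes from 70 to 60, a change of -10. The difference in effect is -20 - (+10) = -30.

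**Equation (2) on the household total.** There is one row per household, and collector gender has no value on that row. If the total is repeated on a female row and a male row, both rows carry the same y and beta2 is exactly 0, whatever dF and dM are.

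**Equation (2) on split minutes.** With F on a female row and M on a male row, and Z = 1 for female, beta1 = dM and beta1 + beta2 = dF. Hence beta2 = dF - dM, which is the quantity wanted.

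**Numerical check.** I simulated 50 treatment and 71 control clusters with 11 households each (332 x 4 / 121 = 10.98). The assumed effects were dF = -20 and dM = -5, and strata were left out.

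- Household total: treatment effect -24.7 (SE 2.5), close to the assumed -25.
- Total repeated on both rows: beta2 = 0.
- Split minutes: beta2 = -15.7 (SE 1.6), against an assumed -15.

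The minutes are illustrative and say nothing about the size of the effect in this trial.

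**Does the trip count fill the gap?** Only partly. A move of trips from women to men would lower it. A move from women to children would not, because both are counted. A shorter walk with the same number of trips would not change it either.

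**The case against.** The strongest reply is that the protocol plainly means the gender of the person collecting, that time is built trip by trip from a roster that seems to show who went, and that an analyst would split it without being told. Much of that stands. It means the defect lies in the specification and probably not in the data. It does not remove the conflict, since the text sends the subgroup analysis to the primary outcomes and fixes this one as a household total.

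A reader might infer more than the documents support:

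- **That equation (2) is the wrong model.** Its form works once the rows are split by gender. The outcome is at fault.
- **That the cluster index on Z rules gender out.** This is probably loose notation. The text names gender as a Z, the listed modifiers include "Education (a binary indicator for above or below median formal education of the household head", a household characteristic, and the treatment indicator appears with both a c and an i index. Correcting the index alone would not help while the outcome is the total.
- **That the test would use the respondent's or household head's gender.** Nothing says so. Sex of respondent appears only in the balance list, struck through.
- **That a shift within the household would go unseen.** The trip count would show part of it.
- **That a formal test is at stake.** The wording is exploratory, and the false discovery rate control covers only the four primary outcomes.

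**Conclusion.** The point holds in a limited form. As defined, the time outcome cannot support an estimate of how the effect differs between female and male collectors, and no other pre-specified outcome supplies it. This follows from the definitions and needs no assumption about effect sizes. The consequence for this trial cannot be sized from the documents; the minutes above only show that one total effect is compatible with gender differences of either sign.

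It would go too far to conclude that the trial cannot answer the question. It probably can, if roster HH-A.4 records each collector's sex. The trip count by women and children suggests this, but the questionnaire is not shown. The four main intention-to-treat analyses do not depend on the point. It should still be settled before analysis, because this is the subgroup question given priority.

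**What to change.** For this analysis only:

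1. **Outcome.** From roster HH-A.4, define minutes collected by female members and by male members of each household on the previous day, with zero where that group made no trip. Keep an adult/child split as exploratory. First confirm that the roster records the collector's sex.
2. **Model.** Fit equation (2) on stacked household-by-gender rows with T, female, T x female and stratum dummies. Index Z at the row level and cluster standard errors on the randomised village cluster.
3. **Strata.** Let the stratum dummies differ by gender (stratum x female). With two rows per household, dummies common to both rows cancel from the within-household contrast, which leaves beta2 unadjusted for strata. That matters because the Randomization Annex gives unequal treatment shares: 8 of 37 clusters in Kasai Central (22%), against 9 of 18 (50%), 20 of 39 (51%) and 13 of 27 (48%) elsewhere. Equation (1) fitted to female minus male minutes gives the same coefficient.
4. **Reporting.** Give the effect on each sum from equation (1) beside the interaction.
5. **Estimand.** State that it is household-level minutes by gender. Households with no members of a group contribute zeros, so composition is mixed with burden.

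The cost is a paragraph in the plan and a few lines of code. No new data are needed if the roster holds the collector's sex. If it does not, the plan should say that gender differences in time cannot be estimated at midline and that the trip count is the only proxy.

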## Sample size and power calculations

In the midline we conduct a village-level survey with the village chief and/or water committee chair in each of the 332 study villages, as well as a household survey from a random sample of 4 households in each village. The objective is to have enough power to estimate initial impact of program implementation, while also helping to finetune the sample size requirements to measure development impacts in the longer-term follow up survey (including generating estimates on the standard deviation and intra-cluster correlation of some of selected health and education measures).

For the midline power calculations, we focus on a primary outcome – whether the household uses an improved water source as their primary source of water. Since the program focuses on villages that have poor water access, we anticipate the level in the control group to be quite low. We also expect a high intra cluster correlation since households in a given village will likely be using the same available water sources as their main water sources.

For these calculations, we limit the risk of Type I errors (false positives) to 5% (alpha = 0.05) and Type II errors (false negatives) to 20% (beta = 0.8). We use the Joint Monitoring Program (JMP)/UNICEF estimate for DRC nationally as an upper bound for improved water access. This is 42%. Since this is a cluster-RCT, we also need to estimate the intra-cluster correlation which is not possible with the available data. Instead we use a conservatively high level of 0.7 given the common infrastructure used in many villages. With 4 households sampled from each village, a 22 percent (or 8-percentage point) increase in access to improved water could be detected using the 121 clusters. Given the large changes anticipated in these operational outcomes, this is expected to be within expectations for the program

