# **Estimation**

We will separately estimate the main impacts of VEA on the outcomes listed above, using the following basic specification:

$y_{ihvc}= +\beta_{1}T_{c}+ \boldsymbol{\gamma X}_{ihvc}+\boldsymbol{\delta Z}_{ihvc}\boldsymbol{+}\varepsilon_{i}$ (1)

where $y_{ihvc}$ is the outcome of interest for respondent *i* in household *h* in village *v* in cluster *c* at the follow-up survey, defined above. $T_{i}$ is the treatment indicator that takes value 1 for clusters that were randomly assigned to participate in VEA (“treatment clusters”) and 0 for otherwise (“control clusters”). $\boldsymbol{X}_{ihvc}$ represents a set of strata-specific dummies where strata are based on province and number of villages in the cluster, which will equal 1 if the household falls in that stratum, and 0 otherwise. $\boldsymbol{Z}_{ihvc}$ is a vector of baseline covariates included in the analysis. Specifically we include gender and age (month) dummies for all <5 child health outcomes, but do not include covariates for other outcomes. $\boldsymbol{\gamma}$ and $\boldsymbol{\delta}$ are vectors of associated strata and covariate coefficients respectively. $\varepsilon_{i}$ is an idiosyncratic error term. Our main parameter of interest is $\beta_{1}$, the intention-to-treat effect (ITT). Standard errors will be clustered at the randomization (village cluster) level.

Our primary outcomes comprise four different measures. Our secondary outcomes comprise a broader range of variables, particularly the health behavior outcome set. To reduce the number of statistical tests and reduce the probability of false positives (Type I errors), when an outcome space is comprised of multiple variables (such as the health behavior outcomes) we combine measures into an index following (Kling, Liebman, and Katz 2007). For our four primary outcomes we use the (Benjamini, Krieger, and Yekutieli 2006) method to control the false discovery rate (FDR) and report adjusted p-values for these primary outcome measures. We do not apply this to secondary (exploratory) variables.

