Since randomization is based on clusters but UNICEF targets are based on villages, it is not possible to force the randomization to select the exact number of UNICEF villages targeted without introducing potential bias. Instead we compare the number of UNICEF target villages per province to the number of treatment villages selected after randomization. In cases where the number of treatment villages is larger than the target, we randomly drop an equal number of program villages from the largest control and treatment clusters until targets are met. For Kongo Central this meant dropping 2 villages and for Kasai this meant dropping 4 villages split equally from the largest treatment and control clusters.

The result of the randomization selection is summarized in the below table:

| **Province** | **Total sampling frame of villages received** | **Treatment villages (clusters)** | **Control villages (clusters)** | **Villages dropped** |
| --- | --- | --- | --- | --- |
| **Kongo Central** | 40 | 20 (9) | 18 (9) | 2 |
| **Kasai** | 98 | 50 (20) | 44 (19) | 4 |
| **Kasai Central** | 81 | 16 (8) | 65 (29) | 0 |
| **South Kivu** | 120 | 60 (13) | 60 (14) | 0 |
| **Total** | **339** | **146 (50)** | **187 (71)** | **6** |
| ***North Kivu*** | *Excluded due to lack of clusters (3) from the province* | | | |

1. Arguably, the proposed mechanisms or channels cannot be identified causally within the current study design. Rather, these will be investigated through qualitative research. [↑](#footnote-ref-1)
2. Unicef. Logigramme Villages et Ecoles Assainis. Guide de Sélection des Villages et des Ecoles. Version février 2014. Fichier .ppt. [↑](#footnote-ref-2)
3. A more detailed description of the sampling and randomization can be found in the Randomization Annex. [↑](#footnote-ref-3)
4. We note that this is a robustness check rather than a formal test to try find spillovers. [↑](#footnote-ref-4)
5. In practice, we find the centroid of all GPS points of program villages that are clustered into an administrative unit and compare this centroid between clusters to assess how close each administrative village is. In some cases, GPS points are clearly inaccurate (e.g. indicating that a program village lies in the water). In these cases, we remove that village GPS from the centroid calculations and rely on the other program villages that are part of the same cluster. [↑](#footnote-ref-5)

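### Exploratory province effects rest on as few as 8 or 9 treated clusters, where ordinary cluster-robust errors are somewhat too small; a few-cluster method should be named for these terms

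*Protocol*

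**What the plan says.** The Subgroup And Spillover analysis section names gender differences in water-collection time as the primary subgroup interest. It then says "We have additional exploratory interest in" four further characteristics, the first being "Province (each of the four provinces". It adds: "Each subgroup analysis will cover the set of primary outcomes described in Section 4". Equation (2) contains a treatment term, a treatment-by-characteristic term and stratum fixed effects, and the coefficient of interest is the interaction, beta_2. The section does not say whether province is tested jointly or contrast by contrast, and it states no variance estimator.

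The Estimation section says, under equation (1): "Standard errors will be clustered at the randomization (village cluster) level". It names no small-sample correction and no reference distribution. False discovery rate control is confined to the tests of the four primary outcomes.

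The results table of the Randomization Annex gives treated and control clusters as 9 and 9 in Kongo Central, 20 and 19 in Kasai, 8 and 29 in Kasai Central, and 13 and 14 in South Kivu. The totals are 50 and 71.

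**The concern.** Cluster-robust errors are reliable when many clusters inform the coefficient being tested. The pooled effect has 121. A province-versus-province contrast draws only on the clusters of the two provinces compared, and the effect within one province only on that province's clusters. The smallest treated groups have 8 and 9 clusters. The usual finite-sample factor and t distribution are set from the overall cluster count, so they barely correct for this. Standard errors for the province terms then come out too small and their p-values too low.

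At stake is over-reading of province differences: an exploratory table might show that the programme worked in one province and not in another more often than its nominal level implies.

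**Working it through.** **Plan's own figure.** The protocol gives no error rate or power for the province analysis, so there is nothing to reproduce. The nominal 5% is taken from the sample-size section and assumed two-sided.

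**Inputs from the protocol.** Cluster and village counts come from the Annex table (146 + 187 = 333 villages). The midline has "a household survey from a random sample of 4 households in each village", so N = 333 × 4 = 1,332. On the intra-cluster correlation the protocol says "Instead we use a conservatively high level of 0.7 given the common infrastructure used in many villages".

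**Inputs assumed.** These are the cluster-size distribution, the split of the correlation between cluster and village, and the usual correction G/(G−1) × (N−1)/(N−k) with t or F on G−1 = 120 degrees of freedom.

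**Step 1: hand check with equal cluster sizes.** Take four province means, one treatment term and three interactions, so k = 8. The correction factor is c = (121/120) × (1331/1324) = 1.0083 × 1.0053 = 1.0137. This raises a standard error by only about 0.7%.

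Let each cluster mean have variance σ². A group of n clusters contributes σ²/n to the true variance. Without correction, the robust estimator has expectation σ²(n−1)/n². Hence:

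- SE ratio = √[c × Σ(n−1)/n² ÷ Σ1/n]
- Satterthwaite df = (Σ1/n)² ÷ Σ[(1/n)²/(n−1)]
- Rejection rate ≈ P(|t_df| > 1.980 × SE ratio), where 1.980 is the 5% critical value on 120 df.

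For Kongo Central, Σ1/n = 1/9 + 1/9 = 0.2222 and Σ(n−1)/n² = 2 × 8/81 = 0.1975. The ratio is √(1.0137 × 0.8889) = 0.949.

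For Kasai Central, Σ1/n = 1/8 + 1/29 = 0.1595 and Σ(n−1)/n² = 7/64 + 28/841 = 0.1427. The ratio is √(1.0137 × 0.8946) = 0.952.

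| Term | SE ratio | df | Rejection of a true null |
|---|---|---|---|
| Kongo Central effect | 0.949 | 16.0 | 7.9% |
| Kasai Central effect | 0.952 | 11.2 | 8.6% |
| South Kivu effect | 0.969 | 24.9 | 6.7% |
| Kasai effect | 0.981 | 36.9 | 6.0% |
| Kasai Central minus Kongo Central | 0.951 | 27.2 | 7.1% |
| Pooled, 50 vs 71, strata ignored | 0.998 | 105.6 | 5.1% |

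So even with equal sizes, errors for the two smallest provinces are about 5% too small and are referred to 120 degrees of freedom in place of 11 to 16. The pooled effect is essentially correct. The province contrast is inflated less than the single-province effects because two provinces contribute to it.

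**Step 2: simulation with unequal sizes.** Equation (2) was simulated with no true difference between provinces, using the Annex counts, 4 households per village, and province or province-by-size stratum effects. Outcome rates were 0.42 or 0.20 in both arms, or 0.20 against 0.60 in every province. The correlation was placed between clusters, within villages, or mixed. There were 4,000 to 6,000 runs per scenario.

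| Test (nominal 5%) | Near-equal sizes | Unequal sizes |
|---|---|---|
| Province-versus-province contrast (beta_2) | 6 to 8% | 6.5 to 12% |
| Single effect, Kongo Central or Kasai Central | 7 to 12% | 7 to 16% |
| Joint 3-df test of equal effects | 8 to 11% | 10 to 19% |

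Standard errors for the Kongo Central and Kasai Central effects were 3 to 6% too small with near-equal sizes, in line with Step 1, and about 8 to 17% too small with unequal sizes.

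**Step 3: which column applies.** The Annex shows that sizes differ, since "we randomly drop an equal number of program villages from the largest control and treatment clusters until targets are met". Mean size also varies between provinces: 38/18 = 2.1 villages per cluster in Kongo Central and 120/27 = 4.4 in South Kivu. How uneven sizes are within a province is not stated, so both columns are kept.

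**Step 4: does a few-cluster method help?** Bias-reduced (CR2) errors with Satterthwaite degrees of freedom brought the one-degree-of-freedom tests to about 3 to 9%, mostly 5 to 6%. Randomisation inference, the wild bootstrap and a corrected joint test were not computed.

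**The case against.** The strongest reply is that the protocol prescribes nothing wrong here. The clustering sentence sits under equation (1), no software or correction is named, and clustering at the randomisation level is compatible with bias-reduced errors or a wild cluster bootstrap. A small-sample refinement for an exploratory interaction could be left to the analysis stage. All of that is true, and it is why the finding is conditional on the usual correction being used. The point survives because this document is itself the pre-analysis plan, clustered errors are the only inference it states, and carrying them over to equation (2) in the ordinary way gives the rates above.

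Some stronger readings are tempting but not supported:

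- A reader might infer that the planned province test has a false-positive rate of 10 to 15%. That range fits a joint test with unequal cluster sizes. The plan names no joint test, and it does not give the size distribution.
- A reader might infer that each interaction coefficient draws on one province only. In equation (2) it is a difference from a reference province and draws on two, so its inflation is milder.
- A reader might infer that decisions on where to continue the programme hang on these tests. No section says so. The analysis is labelled exploratory, and the Introduction says that the midline mainly measures implementation.

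**Conclusion.** The concern holds as a cheap improvement. With the usual correction and 120 degrees of freedom, a nominal 5% test rejects a true null about 6 to 12% of the time for beta_2 contrasts between provinces. The rate is about 7 to 16% for single effects in Kongo Central and Kasai Central, and about 8 to 19% for a joint test. The direction and the low ends follow from the Annex counts and can be checked by hand. The high ends depend on strongly uneven cluster sizes, which are assumed. The pooled intention-to-treat effect and the primary conclusions are untouched; the consequence is limited to over-reading exploratory differences between provinces.

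**What to change.** Add one sentence for the province terms of equation (2): p-values and intervals come from a few-cluster method. Bias-reduced (CR2) cluster errors with Satterthwaite degrees of freedom would serve. So would a wild cluster bootstrap, or randomisation inference suited to the null of equal province effects. Redrawn assignments must respect the strata and the higher control probability in Kasai Central described in the Annex. State that one joint province test by such a method is reported before any single province is read. Keep the planned clustered errors for equation (1).

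The cost is a sentence and readily available software. The downside is wider intervals for the exploratory province estimates.
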